## Abstract

**Background:**

Early graft dysfunction due to preservation/reperfusion injury represents a dramatic event after liver transplantation. Enhancement of donor organ criteria, in order to cope with the ever increasing donor shortage, further increases graft susceptibility to ischemic alterations.

Major parts of post-preservation injury, however, occur at the time of warm reperfusion but not during ischemic storage; successful reperfusion of ischemic tissue in turn depends on an adequate redox and intracellular signal homeostasis. The latter has been shown experimentally to be favorably influenced by oxygen persufflation within short time spans. Thus viability of marginally preserved liver grafts could still be augmented by transient hypothermic reconditioning ***even after ***normal procurement and static cold storage. The present study is aimed to confirm the conceptual expectations, that hypothermic reconditioning by gaseous oxygen persufflation is a useful method to suppress injurious cellular activation cascades and to improve post-ischemic recovery of marginally preserved liver grafts.

**Methods/Design:**

OPAL is a prospective single center randomized proof of concept study, including two parallel groups in a total of 116 liver transplant patients. The effect of an in hospital treatment of the isolated liver graft by 2 hours of oxygen persufflation immediately prior to transplantation will be assesses as compared to standard procedure (cold storage without further intervention). The primary endpoint is the peak transaminase serum level (AST) during the first three days after transplantation as a surrogate readout for parenchymal liver injury. Other outcomes comprise patient and graft survival, time of intensive care requirement, hepatic tissue perfusion 1h after revascularisation, early onset of graft dysfunction based on coagulation parameters, as well as the use of a refined scoring-system for initial graft function based on a multi-parameter (AST, ALT, Quick and bilirubin) score. Furthermore, the effect of OPAL on molecular pathways of autophagy and inflammatory cell activation will be evaluated. Final analysis will be based on all participants as randomized (intention to treat).

**Trial Registration:**

Current Controlled Trials ISRCTN00167887

## Background

Early graft dysfunction due to preservation/reperfusion injury represents a dramatic event after liver transplantation, affecting long term prognosis of graft viability and patient outcome [1,2].

In face of the growing shortage of donor organs, the acceptance criteria for liver retrieval have been expanded torwards the inclusion of of older donors and the use of 'less than optimal' organs. In doing so, the increased proclivity of these organs to ischemia and cold preservation enhances the risk of primary dys- or even non-function (PNF) of the liver after transplantation. While the number of donors aging > 65 years has increase more than ten-fold from 1991 to 2001 in the United Network for Organ sharing as well as the European Liver Transplant registry [3], increased donor age has been incriminated in large series as a prominent factor associated with decreased graft survival [4,5]. A multivariate analysis of 1148 donor livers showed significantly decrease 3 year survival (62%) in livers originating from donors of > 65 years compared to 75% standard criteria donor grafts [6]. Likewise, moderate to severe degrees of fat accumulation, which was present in 12% of all donor livers, was found an independent predictor of increased preservation injury [4]. Thus the challenges rise concerning maintenance and/or restoration of tissue integrity during the storage period.

An elegant means to do so lies in the provision of oxygen during storage using gaseous oxygen application through the vascular system. The method of venous systemic oxygen persufflation [7] is a simple and versatile way to regenerate cellular energy dependent pathways under conditions of relatively low metabolic work load. Any improvement in the preservation of grafts, which were procured from extended criteria donors and/or experienced extended times of preservation represent a valuable advance to enlarge the total number of viable donor organs and to circumvent the need of re-transplantation.

Earlier experimental studies have suggested that major parts of the post preservation injury occur at the time of warm reperfusion but not during ischemic storage and that deleterious priming of the graft during ischemia can be abrogated prior to transplantation by dynamic revitalization techniques at the end of cold storage [8,9], even in liver grafts which were donated after cardiac death [10].

Since successful reperfusion of ischemic tissue most likely depends on an adequate redox and intracellular signal homeostasis, which is favorably influenced by oxygen persufflation within short time spans, viability of long preserved liver grafts is improved by transient hypothermic reconditioning (HR) prior to implantation.

The optimal treatment time for hypothermic reconditioning of initially cold stored livers by gaseous oxygen persufflation has previously been investigated in a preclinical large animal model. One hour of HR already notably improved functional outcome upon reperfusion, but the maximal therapeutic effect was obtained after 2 hours [11]. Thus, 2 hours of end-ischemic oxygen persufflation of cold stored porcine livers significantly improved survival after transplantation [12].

The technique of vascular oxygen persufflation not only maintains cell and organ integrity and function but also enables (to some extend) the repair of damaged structures and restoration of cellular ion and signal homeostasis.

Moreover, it has shown to reverse ischemia induced breakdown of cellular autophagy [13], thus restoring the cell's regenerative capacity upon reperfusion to remove damaged organelles and recycle denaturated proteins [14,15].

Owing to its simplicity and ease of application, oxygen persufflation appears to be a particularly convenient approach, already shown to be safe and easily applicable to the human situation [16].

Based on these promising results, the present clinical trial protocol was designed as a final Proof-of-Concept study aiming to establish oxygen persufflation as valuable adjunct in clinical liver preservation.

## Methods/Design

This is a single center, randomized, controlled, single blind clinical Proof-of Concept study.

Using a two parallel arms approach (treatment/control) the question will be addressed whether a hypothermic reconditioning protocol using 2h of gaseous oxygen persufflation of the isolated liver graft immediately prior to transplantation will improve early graft function upon reperfusion and mitigate adverse effects associated with preservation/reperfusion injury as compared to standard care (simple cold storage without further intervention).

Only patients who meet all inclusion/exclusion criteria are considered to be included in the trial. The inclusion criteria are:

• Men and women beyond 18 years of age

• Resident in Germany

• Scheduled for first liver transplantation and graft already available

• Patient is willing and able to attend regular follow up examinations

• Written informed consent

### Inclusion criteria for the donor liver

• Donor grafts that are offered to the local Transplant clinic for Implantation, i.e. 'organ rescue offers', or donor age above 65

### Main exclusion criteria

Patients presenting with any of the following are not included in the trial:

• Listed as high urgency (HU)

• Participation in this study at an earlier time

• Simultaneous participation in other clinical trial

• Positive test for HIV

• Pregnant or nursing

All patients are observed for seven days following transplantation on a daily basis. Follow up includes additional observations on the day of discharge and 3 month after transplantation. Patients are followed until 3 month after the last patient is randomized for this trial and are asked to attend clinical routine follow up subsequent to termination of the study.

The schedule for study related activities and data collection is listed in table 1.

**Table 1 T1:** Flow chart

	screening	waiting- phase	preoperative	OP	postoperative								follow up (3 month)
						
					D 1		D3	D3	D4	D5	D6	discharge	
Informed consent	X												
In-/ex-clusion criteria	X		X										
Demography	X												
Medical history	X												
Randomisation			X										
BQS/complications			X	X								X	X
Postoperative dialysis					X	X	X	X	X	X	X	X	
Time of mechanical ventilation					X	X	X	X	X	X	X	X	
Laboratory parameters	X		X		X	X	X	X	X	X	X	X	X
SAE			X	X	X	X	X	X	X	X	X	X	
Death				X	X	X	X	X	X	X	X	X	X
Retransplantation					X	X	X	X	X	X	X	X	X

### Objectives and endpoints

It is the aim of the present study to demonstrate the efficacy of short-term oxygen persufflation as end-ischemic adjunct in liver preservation to improve early graft recovery after transplantation.

Serum peaks of liver transaminases are expected to be surrogates of the extent of reperfusion injury and represent the most commonly used parameters for the progression of liver related disease. They correlate well with parenchymal graft injury [17], usually associated with initial liver dysfunction after transplantation in clinical studies [4,18]. Therefore the peak value of systemic aspartate aminotransferase (AST) during the first three days after transplantation has been chosen as the most important primary endpoint of this study. In considering the serum levels during a period of three days it is thought that a more solid basis will be obtained for the judgment of the individual liver under investigation and to alleviate possible skews of single measurements.

Secondary outcomes are death and retransplantation (3 month mortality) as well as time of ICU-stay, time of ventilation and haemodialysis, complication rate, hepatic tissue perfusion 1h after revasularisation, early onset of graft dysfunction based on Quick's value, as well as the use of a refined scoring-system for initial graft function based on a multi-parameter (AST, ALT, Quick and bilirubin) score according to Heise and co-workers [19].

Moreover, pathophysiological, molecular analyses will be performed as to investigate the impact of hypothermic reconditioning on hepatocellular autophagy [13,20] and early pro-inflammatory surface activation (ICAM-1, TLR expression) after reperfusion.

### Sample size calculation

The sample size calculation is performed for the primary endpoint (maximum absolute AST value during the first three days after transplantation) which is analyzed by an exact two-sided Mann-Whitney-U-test. Under the null hypothesis we expect no differences of the primary endpoint distributions for the two groups which translates into a relative effect *p *= 0.5, i.e. it is similarly likely to observe larger/smaller maximum AST values under one or the other group condition. Under the alternative hypotheses larger maximum AST values are on average expected for the standard treatment. For a significance level α = 0.05 (two-sided) and 52 patients per group would be necessary for a power of 0.8 to detect a relative effect of *p *= 0.66 (which is comparable to a mean difference of ~0.6 in units of standard deviations of a standard normal distribution if a parametric location shift (t-test) model would be appropriate). Considering a drop out rate of 10%, 58 patients per group (overall 116 patients) will be required.

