### Randomization and treatment

The randomization will be a stratified 1:1 stratified block randomization with blocks of variable block length with patient-level stratification factor Model for End-Stage Liver Disease (MELD) score (three levels: < 20, 20-30 und > 30). The donor liver is randomized by our study design. Only patients who had given informed consent to participate in the study will be included in the randomization and the study.

Randomization will be technically realized by a web-interface as organized by the Center for Clinical Trials Essen (ZKSE) who will also train the staff in running the software. Moreover, the ZKSE will monitor and control the randomization.

Treatment is restricted to the isolated liver graft after arrival in the transplantation clinic. In the treatment group, donor livers arriving at the hospital will be subjected to 2 hours of venous systemic oxygen persufflation (OP) prior to implantation, while still being stored in ice cold preservation solution as described previously [7,16,21].

In brief, medical grade oxygen gas is passed through a wash bottle and filtered through a membrane with pore size of 5 μm inserted into the inflow line. The filtered and humidified gas is then introduced into the liver by connecting the tubing to a catheter, previously inserted into the suprahepatic caval vein. In order to avoid any kind of barotraumas to the vulnerable hepatovasculature, The applied driving pressure of the gas entering the liver is limited to 18 mmHg, e.g. by means of an interposed pressure relief valve.

The liver is continuously placed immerged in cold preservation solution in a beaker, kept cold by surrounding crush ice (cf. Figure 1).

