### Statistical analyses and data management

The primary endpoint is the maximum absolute AST value (U/l) on one of the first three post-operative days. As the AST distribution is highly skewed a non-parametric statistical procedure, the two-sided exact Mann-Whitney-U-test, is used for the confirmatory analysis. A SAS Macro will be used to estimate the relative effect *p *and to calculate 95% confidence intervals. Though missing data issues pertaining to the primary endpoint should be minimized given the continued monitoring during study conduct, the possibly remaining missing data of the primary endpoint will be replaced by the maximum global (across both groups) AST values mimicking a "worst-case scenario". The impact of other replacement or imputation strategies will be analyzed in sensitivity analyses.

The confirmatory analysis will be performed for the intention-to-treat population (full-analysis set) which includes all patients randomized for whom transplantation has been initiated.

In addition, to address the non-parametric Behrens-Fisher-problem (the sensitivity of the Mann-Whitney-U-test to any differences in distributions including differences in variances) and to integrate the stratum variable "MELD-Score", sensitivity analyses are preplanned using ANOVA statistics.

All secondary endpoints (see above) will be analyzed descriptively as described in the statistics analysis plan.

Data management and statistical analyses will be performed by the Center for Clinical Trials Essen (ZKSE).

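### The stated power of 0.80 with 116 patients holds only if almost all of the 10% drop-outs leave the analysis set, or if about 3% or fewer of the AST values are set to the maximum

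*Protocol article*

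**What the plan says.** The Sample size calculation section fixes the test, "which is analyzed by an exact two-sided Mann-Whitney-U-test", and the level, "For a significance level α = 0.05 (two-sided"). It gives the base size, "52 patients per group would be necessary for a power of 0.8 to detect a relative effect of" 0.66, and explains that effect as "0.66 (which is comparable to a mean difference of ~0.6 in units of standard deviations". It then inflates: "Considering a drop out rate of 10%, 58 patients per group (overall 116 patients) will be required". The Randomization and treatment section sets 1:1 allocation.

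The Statistical analyses and data management section does not remove patients who lack the endpoint. In the confirmatory analysis, "missing data of the primary endpoint will be replaced by the maximum global (across both groups) AST values". The same section expects such gaps to be kept small by monitoring but gives no rate. It limits the confirmatory set to randomized patients whose transplantation was begun. The abstract describes the final analysis more broadly, as covering everyone as randomized.

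**The concern.** The inflation and the analysis rule treat a lost patient differently. Dividing by 0.9 is right when lost patients disappear and the remaining 52 per group carry the undiluted effect. A patient who stays in with the shared maximum still counts in the sample size but says nothing about treatment. The patient ties with imputed patients in the other arm and ranks at the top against nearly everyone else, whichever arm they belong to. When this happens equally in both arms, the difference between the arms shrinks.

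At stake is the one power figure behind the confirmatory test. If it is too favourable for the analysis actually planned, a non-significant result would be read as stronger evidence against the intervention than the design supports. The point concerns power only.

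**Working it through.** **Inputs** (Sample size calculation, unless noted): two-sided level 0.05; power 0.80; relative effect p = 0.66; drop-out 10%; 58 per group, 116 in total; 1:1 allocation (Randomization and treatment); maximum-value rule (Statistical analyses and data management). The share m of patients imputed per arm is not given. It is an assumption here and is varied from 0 to 10%, equal in both arms.

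**1. The plan's own figures.** Noether's formula for the Mann-Whitney test:

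N = (1.960 + 0.842)² / (12 × 0.25 × 0.16²) = 102.2, or 51.1 per group, rounded up to 52.

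Power with 104 patients: Φ(√(3 × 104) × 0.16 − 1.96) = 0.807. Inflation: 52 / 0.9 = 57.8, rounded up to 58. All stated figures reproduce.

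**2. Effect of the maximum rule.** Take one control and one treated patient. Both are observed with probability (1−m)², and the control value is larger with probability 0.66. Only the control value is imputed with probability m(1−m), and it is then larger. Only the treated value is imputed with the same probability, and the control value is then smaller. Both are imputed with probability m², which is a tie and counts one half. So

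p\* = (1−m)² × 0.66 + m(1−m) + m²/2, which gives p\* − 0.5 = (1−m)² × 0.16.

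At m = 10% the distance from 0.5 is 0.81 × 0.16 = 0.1296.

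**3. Power with all 58 per arm analysed**, Φ(√(3 × 116) × (p\* − 0.5) − 1.96). The simulation used 40,000 trials, a normal shift of 0.583 SD (equivalent to p = 0.66), missing values set to the pooled observed maximum, and a tie-corrected rank-sum test.

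| Imputed per arm | p\* | Power, formula | Power, simulation |
|---|---|---|---|
| 0% | 0.660 | 0.847 | 0.862 |
| 2% | 0.654 | 0.818 | 0.831 |
| 3% | 0.651 | 0.802 | not run |
| 5% | 0.644 | 0.768 | 0.781 |
| 7.5% | 0.637 | 0.724 | 0.732 |
| 10% | 0.630 | 0.676 | 0.680 |

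Break-even: (1−m)² = 2.802 / (√348 × 0.16) = 0.939, so m is about 3.1%.

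**4. A 10% loss split between exclusion and imputation.** If a fraction f of the loss is excluded, 116 × (1 − 0.1f) patients are analysed, and the imputed share among them is 0.1(1−f) / (1 − 0.1f).

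| Share of the 10% excluded | Power, formula |
|---|---|
| none | 0.676 |
| one quarter | 0.709 |
| one half | 0.742 |
| three quarters | 0.776 |
| all | 0.808 |

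Interpolating between the last two rows, 0.80 is reached at about 75% + 25% × (0.800 − 0.776) / (0.808 − 0.776) ≈ 94% excluded.

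**5. Sensitivity.** With exactly 6 imputed per arm, simulated power is 0.717. Imbalance moves it either way: 12% imputed in control and 8% in treatment gives 0.81, and the reverse gives 0.54.

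**The case against.** The strongest reply is that the article keeps drop-out and missing AST apart. Patients lost between randomization and surgery fall outside the confirmatory set as the analysis section defines it. The flow chart places randomization before the operation, and the ethics section lets a patient refuse at any time until then. For such losses, dividing by 0.9 is the right step and power is about 0.81. Missing AST among transplanted patients should also be rare: the endpoint is a maximum over three inpatient days with daily laboratory values, so a full 10% is an upper bound. The rate the authors expect may well lie below the 3% break-even.

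This reply stands against a stronger reading that a reader might infer, namely that 116 patients deliver 68% power rather than 80%. The documents do not support that as a flat statement. It needs the whole 10% to be imputed, equally in both arms, and no section says so. Nor do they support a charge of faulty arithmetic, since 52 and 58 both reproduce.

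The reply does not remove the mismatch. Nothing in the article says that the 10% are untransplanted patients, and 0.80 is met only if nearly all of them are. If the abstract's wording governs, untransplanted patients stay in, have no post-transplant AST and receive the maximum, which is the 0.68 case. The full protocol may define the 10%, but the finding does not rest on that gap. It rests on two rules that the article itself states and that do not fit together.

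It is also fair to say that giving both arms one common value is a pre-specified choice, that the article plans sensitivity analyses with other replacements, and that it plans a confidence interval for the relative effect. These limit how badly a null result could be misread. They do not correct the stated power.

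**Conclusion.** The concern holds as a conditional overstatement of power. For a 10% loss balanced between the arms, power with 116 patients runs from about 0.68 (all imputed) to about 0.81 (all excluded). The stated 0.80 lies near the favourable end of that range. If there are no exclusions, it holds up to about 3% imputed per arm and falls to about 0.77 at 5%.

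These figures assume a true relative effect of 0.66 among observed patients, missingness unrelated to the AST value, and equal rates in both arms. Unequal rates could push power above or below the range. The formula and the simulation agree to within about 0.02.

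**What to change.** 1. Align the abstract with the Statistical analyses and data management section, so that one analysis set is defined for the confirmatory test.
2. In the Sample size calculation section, say what the 10% consists of: how much is expected to leave the analysis set before transplantation, and how much is expected to be missing AST inside it.
3. Restate the power of 116 patients under the planned maximum-value rule for that split. If the split cannot be foreseen, give the range of about 0.68 to 0.81 for a balanced 10% loss.

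The cost is a few sentences and possibly a less favourable power figure. Restoring 0.80 in the worst case would take about 78 per group, but that is not proposed, because the worst case is an upper bound. The imputation method can also stay as it is; narrowing it would be a separate trade-off that this point does not require.

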### Randomization and treatment

The randomization will be a stratified 1:1 stratified block randomization with blocks of variable block length with patient-level stratification factor Model for End-Stage Liver Disease (MELD) score (three levels: < 20, 20-30 und > 30). The donor liver is randomized by our study design. Only patients who had given informed consent to participate in the study will be included in the randomization and the study.

Randomization will be technically realized by a web-interface as organized by the Center for Clinical Trials Essen (ZKSE) who will also train the staff in running the software. Moreover, the ZKSE will monitor and control the randomization.

Treatment is restricted to the isolated liver graft after arrival in the transplantation clinic. In the treatment group, donor livers arriving at the hospital will be subjected to 2 hours of venous systemic oxygen persufflation (OP) prior to implantation, while still being stored in ice cold preservation solution as described previously [7,16,21].

In brief, medical grade oxygen gas is passed through a wash bottle and filtered through a membrane with pore size of 5 μm inserted into the inflow line. The filtered and humidified gas is then introduced into the liver by connecting the tubing to a catheter, previously inserted into the suprahepatic caval vein. In order to avoid any kind of barotraumas to the vulnerable hepatovasculature, The applied driving pressure of the gas entering the liver is limited to 18 mmHg, e.g. by means of an interposed pressure relief valve.

The liver is continuously placed immerged in cold preservation solution in a beaker, kept cold by surrounding crush ice (cf. Figure 1).

